## Methods

### Study Design and Setting

The EFFECT study was a 7-week randomized single-blinded placebo-controlled crossover design study. This study consisted of a 1-week run-in period followed by two 1-week intervention periods separated by a 4-week washout period. All participants were asked to consume 1 study snack per day throughout this study, except during the washout period. After completing the run-in period, participants were randomly assigned to the order of snack consumption: control snack followed by walnut snack or walnut snack followed by control snack. All study visits took place at The Ohio State University (OSU).

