**Figure 1 figure1:**
[figure not shown]
Study timeline.

At the beginning of each intervention period (weeks 0 and 5), participants reported to the Clinical Research Center on the OSU campus. At the Clinical Research Center, weight, vitals, and waist circumference were measured, sleep and diet questionnaires were answered, fasting indirect calorimetry was completed, a fasting blood draw was collected, and the meal challenge was administered with subsequent blood draws and indirect calorimetry measurements performed hourly for 5 hours. Additionally, cognitive function was measured both fasting and at 5 hours after the meal challenge, and any updates to medications and supplements were recorded. Each intervention period lasted 1 week and concluded with a study visit (week 1 and week 6). At the week 1 and week 6 visits, weight, vitals, and waist circumference were measured. A fasting blood draw was collected, cognitive function was measured, and updates to medications and supplements were obtained. There was a 4-week washout period between intervention periods. Figure 2 describes the measurements and information collected at each study visit. Participants were supplied with enough study snacks to consume 1 study snack per day until their next study visit. No study snacks were consumed during the washout period. At study visits, this study’s team verbally asked participants about adherence to consuming 1 study snack per day, changes to diet or activity, and changes to medications or supplements.

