#### Biochemical Markers

Glycated hemoglobin was measured using a finger stick. Erythrocyte and PBMC fatty acids will be analyzed. PBMC lipids will be extracted using methanol and chloroform (1:2 v/v) [57] and methylated using 5% hydrochloric acid in methanol [58] as previously described [59]. Erythrocyte fatty acid methyl esters will be prepared using 14% boron trifluoride in methanol and hexane [60] as previously described [61,62]. Gas chromatography with a 30-m Omegawax TM 320 fused silica capillary column (Supelco) will be used to analyze the fatty acid methyl esters. Standards for fatty acid methyl esters (Matreya, LLC and Nu-Check Prep Inc) will be used to determine retention times of fatty acids in the samples as previously described [63].

From blood collected at fasting and postprandial time points, lipid panels were measured at the OSU Wexner Medical Center Hospital Lab. Glucose will be measured using the Glucose Autokit (FUJIFILM Healthcare Americas Corporation), and insulin levels will be measured using the Meso Scale Diagnostics kit. Fasting glucose and insulin levels will be used to calculate estimated insulin resistance using the homeostatic model assessment of insulin resistance [64]. Markers of inflammation, including fasting and postprandial tumor necrosis factor alpha, tumor necrosis factor receptor 2, C-reactive protein, interleukin-6, and soluble intercellular adhesion molecule-1, will be measured at weeks 0 and 5. Fasting soluble CD14, oxidized low-density lipoprotein, and lipopolysaccharide binding protein will also be measured. Tumor necrosis factor α, tumor necrosis factor receptor 2, soluble intercellular adhesion molecule-1, C-reactive protein, interleukin-6, and lipopolysaccharide binding protein will be measured using a highly sensitive Meso Scale Diagnostics kit, and soluble CD14 and oxidized low-density lipoprotein will be measured by ELISA kits (R&D Systems and Mercodia, respectively). Lipopolysaccharide will be measured using Kinetic-QCL, Kinetic Chromogenic LAL Assay, or ELISA LifeSpan BioSciences. Markers of oxidative stress, 4-hydroxynonenal and malondialdehyde, will also be measured by multiplex methods as previously reported [54,65-68].

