### Statistical Analysis

Postprandial cognitive test scores will be compared between the control and walnut group using a 2-sided paired *t* test to account for the cross-over design. To further adjust for covariates, a linear mixed effect model with subject-specific random intercept will be fit on postprandial test score with the following covariates: study group, preprandial test score at week 0 and 6, BMI, age, sex, education level, and depression score. The regression coefficient of this study’s group will be the adjusted difference in postprandial test score between this study’s groups. Potential carryover of treatment effects from the first treatment period to the second period will be assessed by including an interaction between treatment and period in the mixed-effect models. Significant interaction indicates the existence of a carryover effect, in which case we will only use data from the first treatment period to evaluate the treatment effect using a 2-sample *t* test and linear regression models. Analyses for the primary hypothesis will use participants who completed the entire study and will be based on an intention-to-treat principle, regardless of compliance and study group crossover. Sensitivity analyses will be conducted with multiple imputation on missing values for participants who do not complete the entire study. A linear mixed effect model with subject-specific random intercept will be fit on preprandial test score at week 1 and 6 with the following covariates: study group, preprandial test score at day 0 and 35, BMI, age, sex, and education level. The regression coefficient of this study’s group will be the adjusted difference in preprandial test score after a 7-day intervention between study groups. A linear mixed effect model with subject-specific random intercept will be fit on postprandial test score at weeks 0 and 5 with the following covariates: change in plasma sum of ALA+LA during 7-day intervention, BMI, age, sex, and education level. The regression coefficient of plasma sum of ALA+LA will measure the adjusted correlation between postprandial test score and change in plasma sum of ALA+LA.

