A linear mixed effect model with subject-specific random intercept will be fit on the change of endotoxemia during the 7-day intervention with the following covariates: study group, BMI, age, sex, and education level. The regression coefficient of this study’s group will be the adjusted difference in the reduction of endotoxemia between this study’s groups. β*-*diversity of the microbiome community at days 7 and 42 between all pairs of participants will be calculated using the Bray-Curtis dissimilarity measure. Nonmetric multidimensional scaling ordination will be computed, and nonmetric multidimensional scaling plots will be generated to visualize the difference in β-diversity between study groups. Permutation-based ANOVA will be used to compare the β-diversity between study groups. Operational taxonomic units (OTU) abundance will be compared between study groups using paired *t* tests for each OTU, and the *P* values will be adjusted by the Benjamini-Hochberg procedure [76] to control for false discovery rate. A linear mixed effect model with subject-specific random intercept will be fit on postprandial test score with the following covariates: change of endotoxemia during the 7-day intervention, change of OTU abundance during the 7-day intervention, BMI, age, sex, and education level. As the number of OTUs will be very large, exceeding the sample size, a LASSO (Least Absolute Shrinkage and Selection Operator) penalty [77] will be included in the regression model to select significant covariates.

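### The endotoxemia model analyses the 7-day change without the start-of-period level, which gives up precision (not validity) in a non-primary analysis

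*Protocol article*

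**What the plan says.** The design has "two 1-week intervention periods separated by a 4-week washout period", with snack order randomised. At the start of each period (weeks 0 and 5), according to Study Timeline, "a fasting blood draw was collected, and the meal challenge was administered with subsequent blood draws". At the end of each period (weeks 1 and 6): "A fasting blood draw was collected, cognitive function was measured, and updates to medications and supplements were obtained". Under Biochemical Markers, "Lipopolysaccharide will be measured using Kinetic-QCL, Kinetic Chromogenic LAL Assay, or ELISA LifeSpan BioSciences". Start and end samples therefore exist in both periods.

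For endotoxemia, Statistical Analysis specifies a mixed model with a subject-specific random intercept that "will be fit on the change of endotoxemia during the 7-day intervention with the following covariates: study group, BMI, age, sex, and education level". It interprets the result as follows: "The regression coefficient of this study’s group will be the adjusted difference in the reduction of endotoxemia between this study’s groups".

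The 7-day cognitive model in the same section is built differently. It takes the end-of-week fasting score as outcome, and its covariates are "study group, preprandial test score at day 0 and 35, BMI, age, sex, and education level". That model adjusts for the start value; the endotoxemia model does not, and no reason is given. Because the endotoxemia covariates are listed in full, this is a stated choice rather than a detail left to an unseen analysis plan.

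**The concern.** A change score without the start value as covariate assumes that a person who starts one unit higher in one period than in the other also ends one unit higher. For a variable blood marker the within-person relation is usually weaker than that, and the subtraction then carries start-of-period noise into the result.

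The covariates that are listed do not make up for this. Age, sex and education are fixed within a person, and BMI nearly so under the weight-maintenance goal. With complete data they largely cancel from the within-person contrast. The start level differs between a participant's two periods, so it is the covariate that can sharpen the contrast. At stake is a wider confidence interval than necessary for the walnut-control difference in endotoxemia.

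**Working it through.** **The plan's own figure.** No sample size or power is stated for endotoxemia. The only calculation is for the primary cognitive score: (11.0 × 2.8016 / 3.5)² = 77.5, rounded up to 78. It reproduces, but it says nothing about endotoxemia.

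**Inputs.** Taken from the documents: 78 participants, two periods, start and end samples in each, and the covariate list. Assumed: r, over a range, and equal variances of the start and end differences.

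**Formula.** For each participant let S be the walnut-minus-control difference in start level and E the same difference in end level. Each has variance V, and their correlation is r.

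- Planned change-score contrast: Var(E − S) = 2V(1 − r).
- Start-adjusted contrast: V(1 − r²) = V(1 − r)(1 + r).
- Ratio, planned to adjusted: 2/(1 + r).
- End level alone, ignoring the start: V. The planned contrast is noisier than this when 2(1 − r) > 1, that is, when r < 0.5.

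**Results.** The standard-error ratio is the square root of the variance ratio. The simulation is of a 78-person, two-sequence crossover, 6,000 runs per value of r.

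| Assumed r | Variance ratio 2/(1+r) | SE ratio | Simulated variance ratio |
|---|---|---|---|
| 0 | 2.00 | 1.41 | 1.99 |
| 0.2 | 1.67 | 1.29 | 1.66 |
| 0.4 | 1.43 | 1.20 | 1.39 |
| 0.6 | 1.25 | 1.12 | 1.26 |
| 0.8 | 1.11 | 1.05 | 1.10 |
| 0.9 | 1.05 | 1.03 | 1.04 |

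Both estimators were unbiased in the simulation.

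**How the start level is entered.** Stable differences between people cancel from the change but remain in the raw start value. A single raw term therefore gets one slope that mixes the between-person and within-person relations and is pulled away from the within-person slope. Suppose the between-person SD is twice the within-person SD (an assumption), so that the raw start value has variance 4 + 1 = 5 in within-person units. At r = 0 the pooled slope of change on start is about −1/5. The within-person residual is then E − 0.8S, with variance 1 + 0.64 = 1.64 against 2 for the change, a ratio of 1.22. Simulating the random-intercept model with one raw term under this assumption gave 1.27, 1.17, 1.13 and 1.09 at r = 0, 0.2, 0.4 and 0.6; a separate simulation gave about 1.2 at r = 0. The tabulated gains therefore need the within-person slope to be estimated separately, which the mean-plus-deviation form does.

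**The case against.** The strongest reply is that the planned model is valid. Order is randomised, so the contrast of changes is unbiased, and a change score matches the quantity the plan says it wants, a difference in reduction. Endotoxemia is neither the primary outcome nor named in the objectives, and nothing is powered on it. If r is high, the loss is a few per cent. All of this stands. It limits the point to efficiency but does not remove it. With the start level in the model, the group coefficient is the same whether the outcome is the change or the end level, so the plan's interpretation is kept.

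A second reply is that adjustment is not wholly free. The week 5 start value is measured after the first intervention, so adjusting for it assumes that no carryover reaches it. That is fair. Strengths and Limitations already takes four weeks to be sufficient, although Statistical Analysis still plans a carryover test in the mixed models.

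Three stronger readings are tempting, and the documents do not support them.

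- A reader might infer bias because week 0 follows the run-in snack and week 5 follows snack-free weeks. That difference is common to both sequences and cancels from the treatment contrast when they are balanced. Its usual remedy is a period term, which is a separate matter.
- A reader might convert the variance ratios into participants lost. The 78 were set for the cognitive score, so the conversion has no target here.
- A reader might extend the point to other 7-day changes. In the stated models the changes in ALA+LA and in OTU abundance are predictors, and OTU abundance is otherwise compared by paired t tests.

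**Conclusion.** The point holds as a loss of precision in one non-primary model. The planned analysis has between about 2.0 times (r = 0) and 1.05 times (r = 0.9) the variance of a start-adjusted analysis, so its confidence interval is about 41% to 3% wider. Where the trial falls in that range cannot be told from the documents. The relevant r is the correlation left after stable between-person differences are removed, so a high raw correlation across people would not show that the loss is small.

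The figures rest on equal variances of the start and end differences, no carryover into the week 5 start value, and a start level entered so that its within-person slope is estimated. Adjusting is worthwhile because the value is already in hand and the plan's own 7-day cognitive model adjusts for its start score. It is a cheap improvement; leaving the model as it is would not invalidate the result.

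**What to change.** In the endotoxemia model of Statistical Analysis, add the start-of-period endotoxemia level (weeks 0 and 5) as two covariates: the participant's mean of the two start values, and each period's deviation from that mean. Either the change or the end-of-period level may be the outcome. State this before the endotoxemia data are analysed.

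Copying the form of the 7-day cognitive model, with one raw start value, would help but would recover only part of the gain. No new blood draw or assay is needed. The cost is two degrees of freedom and the stated assumption that nothing carries over into the week 5 start value.

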#### Microbiome

Participants were instructed to collect a stool sample on the 1-2 days before or the morning of week 0, 1, 5, and 6 study visits. An Omnigene Gut fecal collection kit (OMR-200, DNAGenotek) was provided with specific instructions for how to store the sample until delivery to the clinic. Total DNA will be isolated using QIAGEN Power Fecal Pro kits and sequenced to a depth of >25 million reads per sample. Microbe or gene abundances will be defined via alignment to reference genomes and de novo assembly.

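### The beta-diversity permutation test does not carry the crossover pairing and, depending on how it is run, may be conservative or short of power

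*Protocol article*

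**What the plan says.** All references are to the protocol article.

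- **Design** (Study Design and Setting): "participants were randomly assigned to the order of snack consumption: control snack followed by walnut snack or walnut snack followed by control snack". Each person therefore receives both snacks.
- **Samples** (Microbiome): participants are told to "collect a stool sample on the 1-2 days before or the morning of week 0, 1, 5, and 6 study visits". Weeks 1 and 6 are days 7 and 42, the ends of the two intervention periods.
- **Distance** (Statistical Analysis), on beta-diversity: "diversity of the microbiome community at days 7 and 42 between all pairs of participants will be calculated using the Bray-Curtis dissimilarity measure".
- **Test** (Statistical Analysis): "Permutation-based ANOVA will be used to compare the β-diversity between study groups". No pairing, permutation stratum, participant term or period term is given.
- **OTU test**, in the next sentence: "abundance will be compared between study groups using paired *t* tests for each OTU".
- **Primary test** (Statistical Analysis): "using a 2-sided paired *t* test to account for the cross-over design". The mixed models there carry a random intercept for each participant.

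The abstract classes the microbiota objective as exploratory. The Objectives section lists it within objective 2.

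**The concern.** At days 7 and 42 each completer provides one walnut sample and one control sample, so 78 participants give up to 78 × 2 = 156 samples in 78 matched pairs. A permutation test is valid when the labels it shuffles are exchangeable under the null. If two samples from one person resemble each other more than samples from two different people, the 156 labels are not freely exchangeable. What is exchangeable is the order of the two snacks within a person, which is what was randomized.

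The other two-period comparisons in the plan respect this, but the beta-diversity sentence does not say that it does. A shift in community composition could then be reported as no difference, beside paired OTU tests on the same samples that do show one. The Background and Discussion offer increased beta-diversity as a possible walnut mechanism, so a falsely negative result here could be read as evidence against it.

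**Working it through.** **1. The plan's own figure.** The only sample-size figure is for the primary cognitive outcome: difference 3.5, SD of the paired difference 11.0, two-sided alpha 0.05, power 80%.

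n = (SD × (z0.975 + z0.80) / difference)² = (11.0 × (1.960 + 0.842) / 3.5)² ≈ 77.5, rounded up to 78.

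This reproduces the stated 78. The exact noncentral t power at 78 is 0.792. No power is stated for beta-diversity, so this figure is not in dispute and does not bear on that test.

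**2. Why the pairing matters.** Take one taxon on the log scale with total variance σ² and within-person correlation (ICC) ρ, and consider the variance of the walnut-minus-control mean difference.

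- True variance with 78 pairs: 2σ²(1 − ρ)/78.
- Variance implied by freely shuffling 156 labels: about 4σ²/156 = 2σ²/78.
- Ratio of true to reference variance: 1 − ρ, so 0.7 at ρ = 0.3 and 0.3 at ρ = 0.7. The reference distribution is too wide, and the test is conservative.
- One day alone, 39 versus 39 different people: 2σ²/39 = 4σ²/78. The reference distribution is right, but the variance is 2/(1 − ρ) times that of the paired comparison, hence at least double.

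**3. Simulation on Bray-Curtis distances.** From the documents: 78 participants, two samples each, and 78/2 = 39 per sequence if allocation is balanced. Assumed: 60 log-normal taxa, the pattern of the shift, no period effect, a 5% test level, and the ICC, which the documents do not give and which was varied. The test statistic is equivalent to the PERMANOVA pseudo-F, with 199 permutations and 600 replicates per cell. At each ICC the shift was set so that within-person permutation has about 80% power.

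| ICC | Type I error: free | Type I error: within-person | Type I error: one day | Power: free | Power: within-person | Power: one day |
|---|---|---|---|---|---|---|
| 0 | 0.048 | 0.047 | 0.052 | 0.813 | 0.797 | 0.385 |
| 0.3 | 0.007 | 0.043 | 0.042 | 0.507 | 0.828 | 0.295 |
| 0.5 | 0.000 | 0.052 | 0.050 | 0.207 | 0.835 | 0.202 |
| 0.7 | 0.000 | 0.050 | 0.052 | 0.007 | 0.823 | 0.130 |
| 0.9 | 0.000 | 0.045 | 0.048 | 0.000 | 0.802 | 0.062 |

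The Monte Carlo standard error is at most √(0.25/600) ≈ 0.02, and about √(0.05 × 0.95/600) ≈ 0.009 near the 5% level.

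**4. Cross-check with other settings.** A second simulation used 100 taxa, 120 to 150 runs per cell and different assumed log-scale SDs.

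- Between-person SD 1.0, within-person 0.6 (ICC 1.0²/(1.0² + 0.6²) ≈ 0.74): free permutation detected 1% and within-person permutation 78%. At a larger shift the figures were 10% and 95%.
- Both SDs 0.6 (ICC 0.5): 33% and 87%.

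The direction and rough size agree with step 3.

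**The case against.** The strongest reply is that the article does not specify free permutation. It specifies no scheme at all, it condenses a longer document, and a permutation stratum is a detail that an SAP may well fix. The pairing stated elsewhere shows a team aware of the design. This stands in part: a reader might infer that the plan prescribes an invalid null, and the text does not support that.

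Second, "microbiome community at days 7 and 42 between all pairs of participants" speaks of pairs of participants, not of samples, and can be read as one distance matrix per day with one sample per person. On that reading the null is valid (simulated type I error 0.042 to 0.052). This also stands, but the crossover is then discarded and the cost moves from validity to power.

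Third, a reader might infer that power is almost lost. That holds for free pooled permutation only at an ICC of about 0.7 or more. At 0.3 to 0.5 the loss is large but not total, and at 0 there is none. The documents give no within-person similarity that would settle which applies.

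Fourth, the outcome is exploratory, and the paired OTU tests would still look for taxon-level shifts.

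What the reply does not remove is that the article fixes the distance, the days and the comparison for this test, yet leaves out the pairing that it states in the very next sentence for the same samples. Except for pooling at an ICC of 0, both natural readings do worse than a within-person permutation.

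**Conclusion.** The point holds as an omission with a concrete better method, not as a proven invalid test. The beta-diversity comparison, as described, does not carry the crossover pairing that the plan uses for its primary and OTU tests.

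- **Pooled samples, free labels:** exchangeability fails and the test is conservative. Power is about 81%, 51%, 21% and under 1% at assumed ICCs of 0, 0.3, 0.5 and 0.7 or more, where within-person permutation has about 80%.
- **Each day alone:** the null is valid, but power is only about 6% to 39% over the same ICC range.

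These sizes rest on the simulated abundances and shift pattern as well as on the ICC, so they illustrate the loss and do not predict it for this trial. The error is towards missing an effect and raises no false-positive concern. The primary cognitive conclusion and the 78-participant calculation are untouched. The change is worth making but not critical.

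**What to change.** State that the day 7 and day 42 samples are analysed together by PERMANOVA on Bray-Curtis dissimilarities. Walnut and control labels should be swapped only within participant (participant as permutation stratum), with participant and period in the model. If the software fits terms in sequence, enter the snack term last. If the full protocol or SAP already says this, confirming it closes the point.

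The cost is one sentence and one software argument. No new data are needed, and the article still describes this analysis in the future tense. The downside is that participants with only one post-intervention sample contribute no within-person information to the test.

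### The exploratory between-snack OTU comparison, as written, makes no use of the week 0 and week 5 stools; it stays unbiased but probably gives up precision for some OTUs

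*Protocol article*

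**What the plan says.** The Microbiome section under Outcomes has participants "collect a stool sample on the 1-2 days before or the morning of week 0, 1, 5, and 6 study visits". Each participant therefore gives a start-of-period and an end-of-period stool for both snacks.

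The Statistical Analysis section first takes β-diversity at the end of each period: "diversity of the microbiome community at days 7 and 42 between all pairs of participants will be calculated using the Bray-Curtis dissimilarity measure". The next comparison is the one at issue: "Operational taxonomic units (OTU) abundance will be compared between study groups using paired" *t* tests, one for each OTU, with false discovery control. That sentence gives no covariate, no change score and no time point.

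Elsewhere the same section does use starting values:
- The endotoxemia model is "fit on the change of endotoxemia during the 7-day intervention".
- The model for cognition after one week adjusts for "study group, preprandial test score at day 0 and 35, BMI, age, sex, and education level".
- The LASSO model for the postprandial score includes "change of OTU abundance during the 7-day intervention, BMI, age, sex, and education level".

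The abstract's Objective paragraph classes the microbiota aim as exploratory.

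**The concern.** A paired test removes stable differences between people. It does not remove slower change within a person over the weeks that separate the two periods. The starting conditions also differ by design. Week 0 follows a week of the run-in snack, while week 5 follows four weeks about which Study Timeline says: "No study snacks were consumed during the washout period". If either source moves an OTU, and the movement lasts to the end of the intervention week, it adds noise to the walnut-minus-control difference. The start-of-period stools carry information about that noise, and the LASSO model already requires their OTU values.

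What is at stake is power. The plan expects more OTUs than participants and controls the false discovery rate, so individual tests need small *P* values. Unused precision means that fewer real shifts are found.

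**Working it through.** **The plan's own figure.** The only sample-size figure is for the cognitive outcome: SD of the paired difference 11.0, difference 3.5, two-sided α 0.05, power 80%. The normal approximation gives n = ((1.960 + 0.842) × 11.0 / 3.5)² = 77.5, rounded up to 78, as stated. With the noncentral *t* distribution, power at 78 is 0.792. The figure reproduces, but it says nothing about OTUs. The document gives no microbiome SD or correlation, so what follows is a range over an assumed correlation.

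**Spacing.** From the collection weeks 0, 1, 5 and 6, the two stools of one period are 1 week apart. Stools from different periods are 4 to 6 weeks apart (1 to 5 is 4, 0 to 5 and 1 to 6 are 5, 0 to 6 is 6).

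**Formulas.** Let w be the correlation of the two stools within a period and b the correlation of stools from different periods, with equal variances. For one OTU, the start-of-period and end-of-period walnut-minus-control differences then have correlation

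ρ = (w − b) / (1 − b).

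Relative to the paired *t* test on end-of-period abundance:
- regression on the start-of-period difference has variance ratio 1 − ρ²;
- a paired test on change scores has variance ratio 2(1 − ρ).

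**Results.** The w and b pairs are examples, and equivalent N is 78 / (1 − ρ²).

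| ρ | example w, b | adjusted ratio | reduction | equivalent N | change-score ratio |
|---|---|---|---|---|---|
| 0 | 0.7, 0.7 | 1.00 | 0% | 78 | 2.00 |
| 0.2 | 0.6, 0.5 | 0.96 | 4% | 81 | 1.60 |
| 0.5 | 0.8, 0.6 | 0.75 | 25% | 104 | 1.00 |
| 0.7 | 0.85, 0.5 | 0.51 | 49% | 153 | 0.60 |

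**Power.** Take an OTU that the plain paired test detects with 80% power, and ρ = 0.5:
- threshold 0.05: (1.960 + 0.842)/√0.75 = 3.235, and Φ(3.235 − 1.960) = 0.90;
- threshold 0.001: (3.291 + 0.842)/√0.75 = 4.772, and Φ(4.772 − 3.291) = 0.93.

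These use fixed thresholds and normal theory. They illustrate the gain and are not the power of the Benjamini-Hochberg procedure.

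**Simulation check.** With 78 participants, 39 per sequence, and 4,000 replicates, the adjusted ratios were 1.02, 0.78 and 0.43, against 1.00, 0.75 and 0.44 from the formula, at (w, b) = (0.7, 0.7), (0.8, 0.6) and (0.9, 0.6). The change-score ratios were 1.98, 1.04 and 0.48, against 2.00, 1.00 and 0.50. The 1.02 shows the small price of estimating a slope that is not needed.

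**The case against.** The strongest reply is that nothing here is an error. A paired *t* test with false discovery control is a valid crossover analysis, the outcome is exploratory, and a condensed article may leave the exact input of each OTU test to a fuller plan. All of that stands, and it limits the point to an efficiency suggestion.

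Four stronger readings are tempting, and the document does not support them:
- **That the plan states the week 0 and 5 stools are left out.** The OTU sentence names no time point. Days 7 and 42 belong to the β-diversity sentence before it. End-of-period abundance is the more natural reading, but a paired test on change is not excluded.
- **That precision is lost for every OTU.** There is a gain only if stools within a period are more alike than stools across periods. The spacing makes that plausible, but no figure is given and the gain may be only 0% to 4%. The run-in against washout contrast matters only for OTUs that the run-in snack shifts, and only if the shift outlasts the following week. It is also a shared period effect, which the regression removes only as far as its slope allows.
- **That both starting stools are pre-treatment.** The week 5 stool comes after randomisation and after the first snack. Using it relies on an adequate washout, which Strengths and Limitations asserts.
- **That the starting stools are wasted.** Change in OTU abundance enters the LASSO model.

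What survives is that the sentence specifies abundance and a test with no covariate, while neighbouring analyses in the same section use starting values.

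**Conclusion.** The point holds as a minor one. As written, the OTU comparison makes no use of the start-of-period stools, and precision is probably lost for OTUs that drift within a person or still reflect the different starting conditions. The variance reduction available is ρ²: nothing at ρ = 0, 4% at 0.2, 25% at 0.5 and 49% at 0.7, with ρ unknown and likely to differ between OTUs. A reader might infer that the between-snack estimate is biased. It is not, because order is randomised and the omission affects only interval width and power. The conclusion assumes that the test uses weeks 1 and 6, that variances are similar across samples, and that the washout is adequate.

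**What to change.** State that the OTU comparison uses the week 1 and week 6 stools. For each OTU, regress the walnut-minus-control difference in end-of-period abundance on the walnut-minus-control difference in start-of-period abundance (weeks 0 and 5). Test the intercept, and apply the planned Benjamini-Hochberg adjustment to those *P* values. Do not substitute simple change scores: they are less precise than the plain paired test whenever ρ is below 0.5, and double its variance at ρ = 0.

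Keep the plain paired *t* test as a sensitivity analysis, including participants who lack a start-of-period stool.

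The cost is a change of analysis wording and one degree of freedom per test. The primary version needs all four stools from a participant and relies on the washout for the week 5 value. No new samples are required.
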